### Outcomes {12}, Participant timeline {13}, Plans to promote participant retention and complete follow-up {18b}

All 100 patients will be observed for 6 months after discharge. The endpoints will be assessed twice, during two control visits, in 1- and 6-months, after enrollment. Patients will be called to schedule the control visit’s date after discharge. Additionally, patients in the IG will receive a notification in their mobile app reminding them about the upcoming ambulatory visits.

Figure 2 shows the recommended SPIRIT figure with the participant timeline. Primary outcome includes both need for rehospitalization and/or urgent outpatient visit and assessed between baseline and 6-month control visit. There are five secondary outcomes related to cardiovascular risk factors control: blood pressure, body mass, nicotinism, dyslipidemia and need for rehospitalization and/or urgent outpatient visit assessed between baseline and 1-month control visit. Detailed target values regarding risk factors control have been presented in Table 1 based on ESC Chronic Coronary Syndrome guidelines [16]. Each value will be categorized as met or not. Secondary outcomes will also include quality of life and depression severity assessment (MacNew, EQ-5D-5L, and DASS-21 questionnaires), cardiovascular risk factors knowledge (CVD risk factors identification recommended BP values, desired lifestyle intervention identification). and return to work in case of professionally active patients.

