**Fig. 2 Fig2:**
[figure not shown]
Recommended SPIRIT figure with participant timeline

**Table 1 Tab1:** Risk factors targets for endpoint assessment

Risk factor		Target level
LDL-c level	No history of MI within 2 years prior	LDL-C lowered by at least 50% from baseline and to <1.4 mmol/L (<55 mg/dL)
	History of MI within 2 years prior	LDL-C of <1.0 mmol/L (<40 mg/dL) in patients who have experienced a second vascular event within 2 years
Body mass index		18.5–24.9 (kg/m^2^)
Systolic blood pressure	General	120–130 mmHg
	Older (aged >65 years)	130–140 mmHg
Nicotinism		Currently non-smoker

*Abbreviations*: *MI* myocardial infarction, *LDL* low-density lipoprotein cholesterol

Further data collection will cover demographic parameters (like sex, age), as well as laboratory test results, and types of prescribed pharmacotherapy.

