#### Secondary outcome measures

##### Cardiovascular risk factors

Blood pressure

All patients at discharge are asked to measure and note blood pressure values daily. The mobile application-derived mean blood pressure values covering 5 days prior to their visits will be averaged for the IG patients. The mean blood pressure values of CG-comprised patients will also be averaged, but based only on the presented written notes. Additionally, meeting guidelines-based recommended values will be checked in both groups. Hypertension is one of the main cardiovascular risk factors, with a significant prevalence of 1.13 billion worldwide [17]. Hypertension control in patients after MI is crucial and correlates with patients’ prognosis [18].

Body mass

All patients will be weighed on admission tl and during control visits 1 and 6 months after discharge. Weight change will be measured. Maintaining a healthy body weight is one of the fundamental aspects of preventing cardiovascular diseases and an essential treatment element after an MI.

Nicotinism

All patients will be asked about smoking on admission and during control visits 1- and 6-months after discharge. Smoking cessation is one of the main goals of patients after MI. Quitting smoking is necessary to reduce the risk of another ischemic incident. It has been documented that smoking cessation results in 50% reduction in the risk of experiencing another MI [19].

Dyslipidemia

All patients after MI will have their cholesterol levels measured during hospitalization. Subsequent cholesterol level measurements will be performed during control visits. According to ESC guidelines, different groups of patients have different LDL cholesterol target values, which should be met during the rehabilitation process [20]. Lowering LDL cholesterol levels correlates with a better prognosis after MI [21].

Quality of life

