## Statistical methods

### Statistical methods for primary and secondary outcomes {20a}, Methods for additional analyses (e.g. subgroup analyses) {20b}, Methods in analysis to handle protocol non-adherence and any statistical methods to handle missing data {20c}, Interim analyses {21b}

In terms of the endpoints, we will look at the frequency of the events 6 months after the discharge, since we believe that due to randomization the groups will be similar at the beginning. No other (including no interim) analyses will be performed in the present study. Regarding secondary endpoints, the change from baseline will be assessed and the frequency of the events in case of rehospitalizations and/or urgent ambulatory visits after 1 month. The distribution of continuous variables will be estimated using the Shapiro-Wilk test. Continuous variables presented with normal distribution will be presented as mean values and standard deviations (SD). All continuous variables presented non-normal distribution will be demonstrated as median values and interquartile ranges. In the case of variables with a normal and non-normal distribution, the groups will be compared using the Student's t-test and the non-parametric Mann-Whitney U test. The comparison of qualitative variables between the groups will be performed using the Fisher exact test. In order to compare changes in the values of continuous variables over time, the analysis of variance will be performed. To compare the outcome of the patients, the Kaplan-Meier estimators will be utilized. For quantitative variables, the change from baseline will be assessed. Additionally, in order to diminish differences in sex and age related to group size, propensity score matching analysis will be performed as well. We also plan to conduct a subanalysis in the group of patients who attended rehabilitation, as well as in those who did not attend.

A per-protocol analysis will be performed after completing all of the follow-up visits. In the analysis, we will include all patients who meet inclusion criteria and sign informed consent regardless of the follow-up completion. Statistical calculations will be performed twice; after obtaining data from the first follow-up visit from all patients and after the final follow-up, 6 months after discharge. In case of missing data, patients will be excluded from the particular analysis.

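### Body mass has two unranked definitions, and one of them, attainment of an absolute BMI band, is insensitive to realistic weight loss

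*Protocol article*

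**What the plan says.** The Outcomes section lists body mass among the secondary outcomes on risk-factor control, refers to Table 1 for target values, and adds: "Each value will be categorized as met or not". The only body-mass entry in Table 1 is a BMI range, "18.5–24.9 (kg/m^2"). It has no category for BMI on admission and no minimum change. The table's title presents these targets as the means of assessing endpoints.

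Under Secondary outcome measures, Body mass, patients are weighed on admission and at both control visits, and "Weight change will be measured".

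The Statistical methods section supports both routes. For categories: "The comparison of qualitative variables between the groups will be performed using the Fisher exact test". For change: "Regarding secondary endpoints, the change from baseline will be assessed", and later "For quantitative variables, the change from baseline will be assessed". No sentence says whether band attainment or weight change is the body-mass endpoint.

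**The concern.** One named outcome has two definitions that can give different answers. A patient of 1.75 m admitted at BMI 33 (about 101 kg) who loses 12 kg reaches BMI 29.1. Weight change records a large success; the band records 'not met'. A patient who drifts from BMI 25.3 to 24.8, about 1.5 kg, records 'met'.

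Two things are at stake. If the band is taken as the endpoint, a weight effect of a size plausible within six months would probably appear as no significant difference. And while the two are unranked, either can be presented as the body-mass result after the data are seen.

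**Working it through.** **Plan's own figure.** None exists for body mass. The sample size of 76 (38 per group) concerns the primary endpoint and is not affected.

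**Step 1: loss needed to enter the band (no distribution needed).** Required loss = 1 − 24.9 / admission BMI.

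| Admission BMI | Loss to reach 24.9 |
|---|---|
| 26 | 4.2% |
| 26.2 | 5.0% |
| 27 | 7.8% |
| 28 | 11.1% |
| 30 | 17.0% |
| 35 | 28.9% |

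A 5% loss changes the score only for patients admitted between about 24.9 and 26.2.

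**Step 2: power under assumed inputs.** The protocol gives no BMI distribution, expected loss or SD of change, so all of the following are assumptions:
- admission BMI normal, mean/SD 27/4, 28/4.5 or 29/5;
- control mean change 0, app effect 0.7 or 1.0 kg/m² (about 2 to 3 kg at 1.75 m);
- SD of change 1.3 or 1.8;
- 50 per arm with no dropout;
- 'met' if 18.5 ≤ BMI < 25.

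Base case (28/4.5, effect 1.0, SD of change 1.3):
- SD of follow-up BMI = √(4.5² + 1.3²) = 4.68.
- Control 'met' = Φ((25 − 28)/4.68) − Φ((18.5 − 28)/4.68) = 0.261 − 0.021 = 24%.
- App 'met' = Φ((25 − 27)/4.68) − Φ((18.5 − 27)/4.68) = 0.335 − 0.035 = 30%.
- Fisher's exact test on 24% vs 30%, 50 per arm: about 7% power.
- t-test on BMI change: effect/SE = 1.0 / (1.3 × √(2/50)) = 1.0/0.26 = 3.85, so power ≈ Φ(3.85 − 1.96) = 97% (96% by simulation).

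Least favourable case for the t-test (effect 0.7, SD 1.8): 0.7/0.36 = 1.94, power ≈ Φ(1.94 − 1.96) = 49% (47–48% by simulation).

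Across all settings (simulation):

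| Quantity | Range |
|---|---|
| Difference in 'met' between arms | 3–7 points |
| Fisher power, band | about 4–8% |
| t-test power, BMI change | about 47–97% |
| App-arm patients admitted at BMI ≥25 losing ≥5%, still 'not met' | 60–77% |
| App-arm follow-up status same as admission status | 82–91% |
| Control patients 'met' who were already in the band on admission | 74–82% |

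**Step 3: a second set of assumptions.** Take admission BMI mean 26–29 and SD 4–5, app-arm mean loss 3–7% (SD 4–5 points), control 0%, and 50 per arm. Band power is then about 7–35%, against about 96% or more for percent weight change. Of those admitted above 24.9 who lose at least 5%, 57–83% score 'not met'. Status agrees with admission in 76–92% of app-arm patients.

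**The case against.** The strongest reply is that weight change is already planned, so the 12 kg loser is not lost to the trial, and that ranking two measures of a secondary outcome can be left to an analysis plan. The first part stands and limits the harm. The second stands only in part: the protocol itself states two definitions of one outcome. The sentence on change from baseline might be read as putting weight change first, but the Outcomes section and the title of Table 1 point to the category.

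It can also be said that attaining a guideline target is a legitimate aim in a trial of risk-factor control. That stands. A patient who gains weight but stays inside the band has maintained a healthy weight and is reasonably scored 'met'. Nor is the BMI row peculiar for lacking a baseline element. The LDL row that has one ("LDL-C lowered by at least 50% from baseline and to <1.4 mmol/L (<55 mg/dL")) requires the absolute level as well, so it is stricter rather than more forgiving, and the blood-pressure and smoking rows have none.

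Two stronger readings are tempting and not supported:
- A reader might infer that chance imbalance in admission BMI biases the comparison or produces false positives. Randomization balances admission BMI in expectation, and Fisher's test already allows for the remaining variation. The cost is precision.
- A reader might infer that most patients with real weight loss count as failures. That holds for those admitted above the band. Among everyone losing at least 5%, including those already in range, the share scored 'not met' is 48–63% under the first set of assumptions and 44–71% under the second, so a majority is not established.

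**Conclusion.** The point holds in a limited form. Body mass is defined twice without a ranking, and the binary definition is insensitive. The loss needed to enter the band is plain arithmetic. The power figures rest on assumed BMI inputs, and the upper end of the band's power (35%) needs the larger assumed losses. The band was far weaker than the continuous comparison in every setting tried. The consequence is a likely uninformative line for one secondary outcome, plus freedom to choose between two results. The primary endpoint, the sample size and the type I error of each single test are untouched. It should be corrected, but no overall conclusion of the trial turns on it.

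**What to change.** In the Outcomes section, Table 1 and the Statistical methods section, name 6-month weight or BMI, analysed as a continuous value adjusted for the admission value, as the body-mass endpoint. Keep attainment of the 18.5–24.9 band as a supportive result, cross-tabulated by admission status so that patients who entered, left or stayed in the band can be seen. The target itself does not change.

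The cost is wording only, since weights on admission and at both visits are already collected. The small downside is that body mass would no longer be led by a single guideline-target percentage like the other risk factors, although that percentage is still reported.

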**Fig. 2 Fig2:**
[figure not shown]
Recommended SPIRIT figure with participant timeline

**Table 1 Tab1:** Risk factors targets for endpoint assessment

Risk factor		Target level
LDL-c level	No history of MI within 2 years prior	LDL-C lowered by at least 50% from baseline and to <1.4 mmol/L (<55 mg/dL)
	History of MI within 2 years prior	LDL-C of <1.0 mmol/L (<40 mg/dL) in patients who have experienced a second vascular event within 2 years
Body mass index		18.5–24.9 (kg/m^2^)
Systolic blood pressure	General	120–130 mmHg
	Older (aged >65 years)	130–140 mmHg
Nicotinism		Currently non-smoker

*Abbreviations*: *MI* myocardial infarction, *LDL* low-density lipoprotein cholesterol

Further data collection will cover demographic parameters (like sex, age), as well as laboratory test results, and types of prescribed pharmacotherapy.

#### Secondary outcome measures

##### Cardiovascular risk factors

Blood pressure

All patients at discharge are asked to measure and note blood pressure values daily. The mobile application-derived mean blood pressure values covering 5 days prior to their visits will be averaged for the IG patients. The mean blood pressure values of CG-comprised patients will also be averaged, but based only on the presented written notes. Additionally, meeting guidelines-based recommended values will be checked in both groups. Hypertension is one of the main cardiovascular risk factors, with a significant prevalence of 1.13 billion worldwide [17]. Hypertension control in patients after MI is crucial and correlates with patients’ prognosis [18].

Body mass

All patients will be weighed on admission tl and during control visits 1 and 6 months after discharge. Weight change will be measured. Maintaining a healthy body weight is one of the fundamental aspects of preventing cardiovascular diseases and an essential treatment element after an MI.

Nicotinism

All patients will be asked about smoking on admission and during control visits 1- and 6-months after discharge. Smoking cessation is one of the main goals of patients after MI. Quitting smoking is necessary to reduce the risk of another ischemic incident. It has been documented that smoking cessation results in 50% reduction in the risk of experiencing another MI [19].

Dyslipidemia

All patients after MI will have their cholesterol levels measured during hospitalization. Subsequent cholesterol level measurements will be performed during control visits. According to ESC guidelines, different groups of patients have different LDL cholesterol target values, which should be met during the rehabilitation process [20]. Lowering LDL cholesterol levels correlates with a better prognosis after MI [21].

Quality of life

Quality of life will be assessed with four questionnaires. The MacNew questionnaire contains 27 questions [22]. The scoring of the MacNew is as follows, the maximum score in every domain is 7 [high quality], and the minimum is 1 [poor quality]. The quality of life is assessed in the context of physical, emotional, and social aspects. The the EQ-5D-5L questionnaire refers to 5 aspects: mobility, self-care, usual activity, pain/discomfort, and anxiety/depression [23]. Every segment is assessed based on a 5 level scale-LEVEL 1: indicating no problem; LEVEL 2: indicating slight problems; LEVEL 3: indicating moderate problems; LEVEL 4: indicating severe problems; LEVEL 5: indicating an inability to/extreme problems. DASS 21 scale will be used to assess depression, anxiety, and stress [24]. The DASS is a quantitative measure of distress along the 3 axes of depression, anxiety, and stress. Seven questions are assigned to every aspect: depression, anxiety, and stress. Each question has 4 possible answers:0-Did not apply to me at all - Never1-Applied to me to some degree, or some of the time - Sometimes2-Applied to me to a considerable degree, or a good part of the time - Often3-Applied to me very much, or most of the time - Almost always

Seven questions are assigned to every aspect: depression, anxiety, and stress.

Higher result in each section contributes to higher severity in depression, anxiety, and stress.

Cardiovascular risk factors knowledge

Cardiovascular risk factors knowledge will be assessed with a previously prepared questionnaire (Supplementary material 2).

Return to work

In the case of previously working patients, the likelihood of returning to work will be assessed, as well as the timing of returning to work will be counseled.

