Additionally, a medical history card will be created for each patient, based on the discharge documents from the hospital. This solution aims for the patient always to have brief information about undergoing coronary interventions. This knowledge might be crucial for the physicians performing subsequent percutaneous coronary interventions (PCI) in the future and could potentially decrease time-to-balloon.

Finally, the application offers a contact panel to text message and call the cardiologists at the hospital. We believe that this will translate into better work organization, better time management (as fewer consultations are likely to be missed by patients), and increased patient safety. All patients randomized to IG will be thoroughly trained in application features and capabilities before discharge.

On the contrary, patients randomized to the CG will be provided with the best available care, based on current guidelines and standards of care [15]. What is more, all patients will be provided with intense medical care supervision, as every patient included in the study will have two additional cardiological consultations.

Rehabilitation programs are recommended for every patient hospitalized due to MI. It has been underlined, that it improves a patient’s prognosis. However, the final decision on the participation is up to the patient. It should be noted, that the study is carried out during the COVID-19 pandemic. Some patients are refusing to participate in the rehabilitation program in fear of infection. However, owing to the randomization, the number of patients who refused to attend rehabilitation is expected to be similar between the groups. Rehabilitation programs include regular cardiac consultations with an experienced physician, psychological sessions, exercise training, stress management programs, and dietary recommendations. The patient is offered versatile support for one year after MI. Patients who refuse to take part in the rehabilitation program are managed by a general practitioner. Owing to the randomization, patients’ distribution is expected to be similar in both groups.

All data implemented into the application was prepared by experienced cardiologists with considerable experience in both, clinical practice as well as eHealth use.

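### Blood pressure is to be analysed as change from baseline, but its outcome is a home average that cannot be obtained before allocation; compare follow-up values instead

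*Protocol article*

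**What the plan says.** Under Outcomes, the protocol article lists blood pressure among the secondary risk-factor outcomes. Statistical methods then gives the general rule: "Regarding secondary endpoints, the change from baseline will be assessed". Later in the same section it adds: "For quantitative variables, the change from baseline will be assessed".

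The Cardiovascular risk factors subsection describes how blood pressure is obtained: "All patients at discharge are asked to measure and note blood pressure values daily". In the intervention group (IG), "The mobile application-derived mean blood pressure values covering 5 days prior to their visits will be averaged for the IG patients". In the control group (CG), "The mean blood pressure values of CG-comprised patients will also be averaged, but based only on the presented written notes". A second use of the same data follows: "Additionally, meeting guidelines-based recommended values will be checked in both groups".

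The neighbouring risk factors each have a hospital value. For weight the text reads "All patients will be weighed on admission tl and during control visits 1 and 6 months after discharge". Smoking is asked about on admission, and cholesterol is measured during the stay. The blood-pressure paragraph names no such value.

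On timing, the allocation section has the group disclosed to the physician once consent and the initial documentation are complete. The Intervention description adds: "All patients randomized to IG will be thoroughly trained in application features and capabilities before discharge".

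**The concern.** A change score needs a first value taken before treatment can act, and preferably by the same method as the second. For weight, smoking and cholesterol the text supplies a hospital value. For blood pressure, the described series of readings starts after the patient's group is known and, in the IG, after app training. Whoever runs the analysis must therefore choose a baseline that the text does not name, and the two available kinds behave differently:

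- **An in-hospital reading** comes from the acute infarction stay and is not a home average.
- **The first home readings** match the outcome in method but come after randomisation.

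At stake is the precision of the continuous blood-pressure comparison in the first case, and in the second also what that comparison estimates. Blood pressure matters here because the hypothesis concerns risk-factor management, and the allocation section gives adjustment of blood-pressure treatment as its example of a decision prompted by app data.

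**Working it through.** **Order of events, from the text**

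1. Consent and initial documentation, in hospital (allocation section).
2. Allocation disclosed (same section).
3. IG patients trained in the app, before discharge (Intervention description).
4. Discharge; patients are asked to start daily home readings (Cardiovascular risk factors).
5. Control visits at 1 and 6 months; averaged home readings form the outcome (Outcomes; Cardiovascular risk factors).

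The described home readings begin at step 4 and allocation is known at step 2. A baseline by the outcome's method therefore cannot precede allocation.

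**Case A: baseline is an in-hospital reading taken before step 2**

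The documents give no SD, effect size or correlation for blood pressure, so there is no figure of the plan to reproduce. The stated sample size concerns the primary endpoint and plays no part here. Let r be the correlation between the in-hospital reading and the follow-up average, and assume equal SDs. Relative to comparing follow-up values alone (variance 1):

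- change score: 2(1 − r)
- follow-up value adjusted for the baseline: 1 − r²

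| r (assumed) | Change score: variance | Change score: SE | Adjusted: variance | Adjusted: SE |
|---|---|---|---|---|
| 0.1 | 1.80 | 1.34 | 0.99 | 0.99 |
| 0.2 | 1.60 | 1.26 | 0.96 | 0.98 |
| 0.3 | 1.40 | 1.18 | 0.91 | 0.95 |
| 0.5 | 1.00 | 1.00 | 0.75 | 0.87 |
| 0.7 | 0.60 | 0.77 | 0.51 | 0.71 |

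The change score breaks even with the follow-up value at r = 0.5. Against the adjusted comparison it never wins: 2(1 − r) − (1 − r²) = (1 − r)², which is never negative.

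This does not depend on equal SDs. With k = baseline SD / follow-up SD, the change score has relative variance 1 + k² − 2rk, and the difference from 1 − r² is (k − r)², again never negative. Only the break-even point against follow-up alone moves, to r = k/2.

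On bias: if the reading is taken in the same way in both arms before disclosure, its expected value is equal in the two arms. The move from hospital to home shifts both arms' mean change alike and cancels in the contrast. Only precision is affected.

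**Case B: baseline is an early home average**

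Let the difference between arms at follow-up be D, and let a fraction f of it already be present in the early home readings. The change-score contrast then estimates D − fD = (1 − f)D. The documents give no basis for a value of f. Any f above zero shrinks the estimate, and the baseline is in any case a post-randomisation value.

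**Unaffected analysis**

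Classifying systolic pressure against the Table 1 target as met or not, and comparing arms with the Fisher exact test, needs no baseline.

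**The case against.** The strongest reply is that this is a condensed article. The assessment schedule is in Figure 2, which was not available for this review, and the contents of the initial documentation are not listed. A reader might infer from the blood-pressure paragraph that no usable baseline exists. The documents do not support that: a pre-allocation hospital reading may well be recorded. What stands regardless is that any such reading is not a home average, and any home average comes after allocation.

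A reader might also infer that a hospital baseline biases the comparison. It does not, if it is taken alike in both arms before disclosure. Nor may the precision loss be taken as established, since at r = 0.7 the change score gains on the follow-up value alone. The case for replacing it rests on adjustment being at least as precise at every r.

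It is fair to add that the change-from-baseline rule is a blanket one, that the blood-pressure paragraph itself speaks of averages and target attainment and not of change, and that nothing in the text proposes early home readings as the baseline. Even so, the rule is stated twice, the second time for quantitative variables, and averaged blood pressure is one. The text also does not exclude the home option.

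Finally, a new standardised reading before allocation would come too late. The version is dated 21 February 2022, about 14.7 months after recruitment began; at the stated rate of about 7 patients a month that is 14.7 × 7 ≈ 103, against 100 planned, with recruitment due to close on 31 March 2022. This objection is accepted, and the fix asks for no new measurement.

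**Conclusion.** The point holds for the continuous blood-pressure analysis only. The plan applies change from baseline to an outcome for which a baseline by the same method cannot precede allocation, and it does not say which other value serves.

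- With a hospital reading the cost is precision, not bias. With equal SDs, the standard error relative to the follow-up value alone ranges from 34% larger at r = 0.1 to 23% smaller at r = 0.7. Every value of r here is an assumption.
- With early home readings the estimate is reduced by whatever part of the effect has already appeared; its size cannot be given.

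The adjusted follow-up comparison is at least as precise as the change score at any correlation. The primary endpoint and the met/not-met blood-pressure analysis are untouched, so this is a worthwhile correction to one secondary endpoint and no threat to the trial. The different recording source in the two arms (app or written notes) is a separate matter that this change does not address.

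**What to change.** In Statistical methods, exempt blood pressure from the change-from-baseline rule and add, for example:

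> For blood pressure, the arms are compared on the 6-month average, and likewise on the 1-month average, by linear regression adjusted for an in-hospital blood pressure recorded before allocation was disclosed, where one is available. Home readings taken after discharge are not used as baseline.

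Two details belong with it. Name the in-hospital reading to be used, under the same rule in both arms. And say that patients without one stay in the comparison (for instance with a missing-value indicator for the covariate), since the plan's exclusion rule for missing data would otherwise drop them. If hardly any such readings exist, compare the follow-up values unadjusted.

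The cost is a few sentences, a look through existing records, and the ethics-committee notification that the plan already requires for amendments. No new measurement or visit is needed. The change should be made before the first planned calculations, which follow the last patient's 1-month visit. The small downside is that this one endpoint is analysed slightly differently from the other quantitative variables.
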